## Abstract

**Background:**

Strokes pose a particular challenge to the health care system. Although stroke-related mortality has declined in recent decades, the absolute number of new strokes (incidence), stroke deaths, and survivors of stroke has increased. With the increasing need of neurorehabilitation and the decreasing number of professionals, innovations are needed to ensure adequate care. Digital technologies are increasingly used to meet patients’ unfilled needs during their patient journey. Patients must adhere to unfamiliar digital technologies to engage in health interventions. Therefore, the acceptance of the benefits and burdens of digital technologies in health interventions is a key factor in implementing these innovations.

**Objective:**

This study aims to describe the development of a discrete choice experiment (DCE) to weigh criteria that impact patient and public acceptance. Secondary study objectives are a benefit-burden assessment (estimation of the maximum acceptable burden of technical features and therapy-related characteristics for the patient or individual, eg, no human contact), overall comparison (assessment of the relative importance of attributes for comparing digital technologies), and adherence (identification of key attributes that influence patient adherence). The exploratory objectives include heterogeneity assessment and subgroup analysis. The methodological aims are to investigate the use of DCE.

**Methods:**

To obtain information on the criteria impacting acceptance, a DCE will be conducted including 7 attributes based on formative qualitative research. Patients with stroke (experimental group) and the general population (control group) are surveyed. The final instrument includes 6 best-best choice tasks in partial design. The experimental design is a fractional-factorial efficient Bayesian design (D-error). A conditional logit regression model and mixed logistic regression models will be used for analysis. To consider the heterogeneity of subgroups, a latent class analysis and an analysis of heteroscedasticity will be performed.

**Results:**

The literature review, qualitative preliminary study, survey development, and pretesting were completed. Data collection and analysis will be completed in the last quarter of 2023.

**Conclusions:**

Our results will inform decision makers about patients’ and publics’ acceptance of digital technologies used in innovative interventions. The patient preference information will improve decisions regarding the development, adoption, and pricing of innovative interventions. The behavioral changes in the choice of digital intervention alternatives are observable and can therefore be statistically analyzed. They can be translated into preferences, which define the value. This study will investigate the influences on the acceptance of digital interventions and thus support decisions and future research.

**International Registered Report Identifier (IRRID):**

DERR1-10.2196/46056

## Introduction

### Background

Strokes pose a particular challenge to the health care system. Although stroke-related mortality has declined in recent decades, the absolute number of new strokes (incidence), stroke deaths, and survivors of stroke has increased [1]. Approximately 40% of patients with stroke present with persistent cognitive, perceptual, and participative disabilities [2,3]. Stroke is the second leading cause of acquired disability [4]. Neurorehabilitation reduces disability and improves functional outcomes [5]. Stroke-related limitations are treated in neurorehabilitation. Most recovery of functions is achieved in the subacute phase (3-6 months after the stroke event) [6]. Neurorehabilitation is a combination of various disciplines [7]. Because of the need for a comprehensive therapy approach, strokes are one of the most cost-intensive diseases in the German health care system, with current treatment costs of approximately €43,000 (US $48,040.40) per patient [8].

### Objectives

With the increasing need of neurorehabilitation and the decreasing number of professionals, innovations are needed to ensure adequate care [9]. Digital transformation has opened avenues for improving services, products, and interventions through the increased use of digital technologies [10,11]. In the project *evidence-based robotic assistance in neurorehabilitation* (E-BRAiN), a robot was developed to support daily therapy practice [12]. Researchers investigated the use of the humanoid robot “Pepper” by SoftBank Robotics owing to interaction [13], motivation, software and hardware capabilities, and acceptance. To decide on implementing innovative therapies, decision makers should consider the trade-offs that patients are willing to accept [14]. Discrete choice experiments (DCEs) are a way to identify trade-offs by analyzing preferences [15]. The acceptance of new therapies is a key success factor and is determined by the fulfillment of needs [16-18]. When acceptance information is considered in decision-making, the utility of care decisions can be maximized in the short term [19,20], can strengthen patient orientation and adherence in the intermediate term, and can improve clinical effects in the long term. Financially, the health care system can benefit from faster and more efficient therapeutic outcomes [21,22].

## Methods

### Ethics Approval

The preference survey instruments, informed consent form, and study design were reviewed and approved by the ethics committee of Hochschule Neubrandenburg (HSNB/177/21). The study considers the Declaration of Helsinki, the Deutsches Bundesdatenschutzgesetz (the German Data Protection Act), the European privacy policy, and Guideline on Good Clinical Practice (CPM/ICH/135/95) regarding the obligation to report serious adverse events.

### Informed Consent, Participation, and Dissemination

Participant confidentiality was ensured by pseudonymization of the qualitative interview recordings and will be ensured by anonymizing the data from the quantitative survey (DCE). All participants have provided informed consent in the completed qualitative interviews. Informed consent is also obtained in the quantitative survey. Participants have the right to withdraw from the study at any time and without giving reasons and to request the deletion of the collected data at any time during the survey. All participants will be informed on the opening page of the web-based questionnaire that participation is voluntary. All identifiable details will be removed during future dissemination of findings and in presentations and publications. Researchers’ contact information is provided on the last page in case the participants have questions. The participants can contact the researchers directly by phone or via a contact email address. The results of this study will be presented at national and international conferences and published in peer-reviewed journals.

### Research Questions and Study Aim

This ongoing study will address the following question: Which criteria of digital technologies impact patient and public acceptance? The aim is to investigate patient and public preferences to generate information on acceptance and analyze the value of digital interventions. Preference evidence is a series of observable human behaviors that can be analyzed by the choices individuals make between alternative health states, health services, or health interventions. Choices define the value of attributes and alternatives in health care.

Acceptance is a requirement for active patient engagement and thus for efficiency (the greatest possible result with the least possible effort) and effectiveness (ability of the intervention to positively improve patients’ state of health in a targeted manner). To obtain information on acceptance, it is necessary to understand the trade-offs that patients make by weighing the advantages and disadvantages of therapy options using digital technologies. We also ask whether patients would accept a humanoid robot in neurorehabilitation. Our primary objective is to weight the criteria that impact patient and public acceptance. Secondary objectives include (1) a benefit-burden assessment (estimation of the maximum acceptable burden of technical features and therapy-related characteristics for the patient or individual, eg, no human contact), (2) overall comparison (assessment of the relative importance of attributes for comparing digital technologies), and (3) adherence (identification of key attributes that influence patient adherence). Our exploratory objectives include (1) heterogeneity assessment (how preferences differed based on participant characteristics) and (2) subgroup analysis (to explore and explain heterogeneity based on the correlation between therapy preferences and participants’ sociodemographic information, experience-based treatment history, and attitudes). Our methodological aims are to investigate the use of DCE and the impact on data quality, preferences, and choice consistency.

The following assumptions and hypotheses will be examined:

Patients engage in a health care process to meet their needs. Health-related needs include therapy outcomes. Therapy outcomes can be measured by goal achievement. Therapy outcomes influence the choice of intervention.H1: The higher the expected success rate, the higher the probability of choosing an alternative.H0: The success rate of an intervention has no influence on the probability of choosing an alternative.Needs involve technical aspects of digital technologies. Undesirable features will have a negative impact on the decisions.H1: The more burdensome or worse a technical aspect is rated, the lower the probability of choosing an alternative.H0: The rating of a technical aspect has no influence on the probability of choosing an alternative.The complete absence of human contact has a negative effect on the decision.H1: The fewer the opportunities for human contact, the lower the probability of choosing an alternative.H0: The opportunity for human contact has no influence on the probability of choosing an alternative.Digital technologies should have certain characteristics according to the goals of a digital transformation (eg, flexibility, adaptability, participation, and empowerment). Characteristics that do not condition flexibility, adaptability, participation, or empowerment negatively impact patients’ therapy decisions.H1: The fewer the goals of the digital transformation that can be achieved by the digital technology, the lower the probability of choosing an alternative.H0: Flexibility, adaptability, participation, and empowerment have no influence on the probability of choosing an alternative.Interventions should be individualized for patients in a patient-centered health care system. Patients’ preferences differ with respect to their characteristics (sociodemographic characteristics, clinical and digital experiences, attitudes, expectations, norms, behaviors, and abilities).H1: The less patient centered an intervention is, the lower the probability of choosing an alternative.H0: The characteristics of different patients have no influence on the probability of choosing an alternative.

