### Elicitation Tasks

The challenge in a DCE is to dissolve the response uncertainty and to trace the preference information back to the individual attributes through repeated choice tasks, with participants “forced” to make a decision between digital therapies. For the professional group, there was no choice available within the choice task. The underlying choice task is a ranking task, which follows a fixed procedure. The choice starts with the selection of the best alternative among 3 choices. The choice is iterated with the remaining 2 so that a complete ranking is achieved. Thus, the DCE uses a best-best choice format [51].

Participants’ willingness to choose the digital therapy was determined by the following follow-up question: “Would you really choose the previously selected digital therapy in real life to improve your health?” Recently, the dual response “none” has been established as a variant in choice experiments [52,53]. A dual response of “none” asks for 2 responses for each task: one choice between the available product alternatives and one between the “none” concept and the previous alternatives. Essentially, it is a choice between the most preferred alternative and none. If participants would actually buy or take the alternative, they would not prefer none, but if they would not buy or take the alternative, they would prefer none to the given alternative [54]. The dual response “none” design takes more time to answer and is an increase in analysis effort owing to a complex design. However, more information is generated, which makes the design more efficient and powerful. Estimation errors are reduced, and the underlying model estimate is not significantly changed [52]. This design provides a higher resolution for individual-level preferences. As there is less “missing” information when participants select “none” as their preferred alternative, more information is available for individual-level modeling [54]. The final survey instrument comprised 6 choice tasks. The number of choice tasks was determined by the underlying experimental design, possible number of participants, and information received per task. No names, brands, or companies were named in the presentation of the choice tasks; therefore, the tasks were unlabeled. In addition, unlabeled alternatives were preferred because the study objectives were to estimate the marginal rates of substitution and value equivalents for therapy attributes [18].

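### Fifth hypothesis pair: H0 concerns respondents' characteristics and H1 concerns patient-centredness of the intervention, so rejecting H0 would not support H1

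*Protocol article*

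**What the plan says.** The Protocol article, Research Questions and Study Aim, lists five hypothesis pairs to be examined.

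- **Fifth pair.** The premise is that "Patients’ preferences differ with respect to their characteristics". The alternative is "The less patient centered an intervention is, the lower the probability of choosing an alternative". The null is "The characteristics of different patients have no influence on the probability of choosing an alternative".
- **Second pair.** The alternative is "The more burdensome or worse a technical aspect is rated, the lower the probability of choosing an alternative", and its null likewise refers to the rating of a technical aspect.
- **Fourth pair.** The alternative is "The fewer the goals of the digital transformation that can be achieved by the digital technology, the lower the probability of choosing an alternative", against the null "Flexibility, adaptability, participation, and empowerment have no influence on the probability of choosing an alternative".

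Elicitation Tasks says that no brands or companies were shown and "therefore, the tasks were unlabeled". Each task has a forced ranking of three alternatives, followed by a question on whether the respondent would really take the chosen one (dual-response none). Table 1 defines seven attributes, five of them technical. The exploratory objectives and the Statistical Analyses section plan to study how preferences differ by respondent characteristics, using mixed logit, latent classes and a group covariate.

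**The concern.** A test supports its alternative only if the null and the alternative concern the same quantity. In the fifth pair they do not. Anyone who follows the plan literally would find some difference between respondents, reject the null, and report that less patient-centred interventions are chosen less often. The data would not bear on that statement. The article intends its results to inform development, adoption and pricing decisions, so a claim about individualised care resting on this pair would be unsupported.

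The second and fourth pairs raise a milder form of the same question. One refers to a rating and the other to a number of goals, and the article does not say which measured variable or attribute levels carry either.

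**Working it through.** The article gives no figure on this point to reproduce. The check is a comparison of the texts, followed by a small calculation of what the design can identify.

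**1. Are the fifth null and alternative complementary?** Two cases show that they are not.

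- All respondents share the same preferences, and all avoid impersonal interventions. The alternative is true and the null is also true.
- Older respondents refuse every digital therapy more often, and nobody cares about patient-centredness. The null is false and the alternative is also false.

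The premise of the pair is a third statement: attribute effects differ by characteristic, which is an interaction.

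**2. Does the design vary patient-centredness?** The Table 1 attributes are explanation of exercises, information, contact with professionals, patients' choice, data processing, copayment and therapy success. Some may relate to patient-centredness, but none is defined as it.

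**3. Can the fifth null be rejected?** Take three unlabelled alternatives with utilities V_j and P_j = exp(V_j) / Σ exp(V_k). For illustration, assume V = (0, 0.5, 1.0), a binary characteristic z and an effect size of 0.8. These values are not in the article.

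| Model | z = 0 | z = 1 |
|---|---|---|
| Main effect: V_j + 0.8z | 0.186 / 0.307 / 0.507 | 0.186 / 0.307 / 0.507 |
| Interaction: 0.4z added per step, V = (0, 0.9, 1.8) at z = 1 | 0.186 / 0.307 / 0.507 | 0.105 / 0.259 / 0.636 |
| Best alternative against none, with main effect | 1/(1+e^−1.0) = 0.731 | 1/(1+e^−1.8) = 0.858 |

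In the first row the factor exp(0.8z) appears in every numerator and in the denominator, so it cancels. A simulated information matrix (1000 respondents, 6 tasks, 3 alternatives, one attribute) agrees. Its diagonal is 570.07 for the attribute, 0 for the main effect of z and 281.31 for the interaction, with rank 2 of 3. The main effect is therefore unidentified in the forced choice, but it is identified in the none question, and the interaction is identified in the forced choice.

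**4. Why scale matters for the remedy.** In the interaction row the step size goes from 0.5 to 0.9, and 0.9 / 0.5 = 1.8. With one attribute this cannot be told apart from the same preferences answered with 1.8 times the scale (less random error). In general, if one group has coefficients λβ, the interactions equal (λ − 1)β, which is non-zero even though the trade-offs are the same. With several attributes the two can be separated, because scale multiplies all coefficients by one factor.

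**5. Second and fourth pairs.** Textbox 1 lists a Likert item on therapy goals, a ranking of transformation goals, and questions on experience with and attitudes to digital technology. It lists no rating of the technical attributes. The goals named in the hypothesis, in Development of Attributes and Levels, and in Textbox 1 are not the same list, and no section assigns attribute levels to goals. Inferring which level is worse from the fitted coefficients and then testing whether worse levels are chosen less would be circular.

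**The case against.** A reader might infer more than the documents support, in three ways.

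- **The fifth null holds by construction because the tasks are unlabelled.** This is true only of a main effect in the forced choice. The null does not restrict itself to main effects, the premise speaks of differing preferences, and the planned heterogeneity analyses and the none question can both reject it.
- **The second and fourth hypotheses have nothing in the design that varies.** Five technical attributes vary, and four of them include a level at which the feature is absent. Level-wise tests are available from the planned models.
- **The goal count can only be none or one.** That holds within the patients' choice attribute alone. Other attributes, such as information in therapy, may also serve goals, so the number can differ between alternatives once a mapping exists.

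It can also be said in the plan's favour that a fuller protocol or questionnaire may contain the rating or the mapping, that the primary objective is to weight criteria, that heterogeneity is labelled exploratory, and that the sample size does not rest on these tests. All of this stands, and it limits the second and fourth pairs to a matter of wording. It does not repair the fifth pair: the mismatch is between two printed sentences, and a fuller document could only correct it by changing one of them.

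**Conclusion.** The fifth pair is wrong as written. Its null can be rejected, but the rejection would be evidence that respondents differ, not that less patient-centred interventions are chosen less often. This rests on the text alone and on no assumed number; the illustrative coefficients serve only to show which effects can be identified.

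The size is one mismatched pair out of five, plus two pairs that the article does not link to a defined rating or goal mapping. Design, data and coefficient estimates are unaffected. What is affected is the conclusion that could be drawn on individualised care.

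**What to change.** **Fifth pair.** Restate it to match its own premise. H0: all interactions between attribute levels and the named characteristics are zero. H1: at least one is not. Test them jointly in the planned models with scale differences between groups taken into account. One way is to compare a model in which groups differ only by a scale factor with one in which all level coefficients may differ; the Abstract already plans an analysis of heteroscedasticity. Draw no conclusion on patient-centredness from this test.

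**Second and fourth pairs.** Replace the rating and the goal count with attribute-level contrasts named in advance, for example against the levels with no information, no contact or no influence. State the expected direction of each before the results are seen. Make each H1 the proper alternative to its H0: for example, H0 that all contrasts are zero and H1 that at least one differs in the expected direction. An H1 that every level is preferred would not do, because it is not the negation of all being equal.

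**Cost.** Rewording of three pairs and a short list of contrasts. No new data, no change to the survey, and the tests come from models already planned.

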### Target Population

We include two study populations: (1) an experimental group (patients with stroke) and (2) a control group (the general population). Only individuals diagnosed with a stroke will be included in the experimental group. For both groups, only individuals aged ≥18 years, who reside in Germany, and who can read and understand German will be included. Limitations in recruitment were expected because of the COVID-19 pandemic at the beginning of the study and during the development of the experiment. Therefore, we decided to include a control group.

### Overall Project Design

Both qualitative and quantitative methods are used in this health preference research (HPR) study. A completed qualitative prestudy was used to identify which decision criteria patients consider when choosing innovative therapy options using digital technologies. Furthermore, the impact of these attributes will be determined in a quantitative survey using a DCE. DCE is a stated preference method for economic evaluation [23,24]. This DCE will be used to analyze how patients define the “value” of a digital technology. The analysis is performed using repeated choices between hypothetical therapy alternatives with different attribute levels [25]. The choices can identify which attributes and levels are preferred. Patient benefit derives from preferences, and thus, the benefit can also be defined as value [26]. DCE is a preference elicitation method [27-29]. The use of such choice experiments is also presentive in medicine [30,31]. There are many guidelines and recommendations for the DCE [32,33]. The increasing popularity of DCE reinforces the intention in this study. This paper describes the protocol of the DCE to investigate patient and public acceptance of digital technologies in health care. This paper also describes the methodology used in our ongoing work.

